## STUDY POPULATION

### Population

Patients meeting the criteria for SMI (Delespaul et al., 2013) that are indicated for generic FACT care will be recruited at the participating mental health centres. Male and female patients between 18 and 65 years old meeting the criteria for having a SMI will be included if they are expected to be in FACT care for the next 18 months and are able to understand and sign informed consent.

### Inclusion criteria:

- Age between 18 – 65 years
- Having a severe mental illness: (1) a diagnosable mental, behavioral, or emotional disorder according to the diagnostic criteria specified within the DSM-5, (2) that is associated with serious social and/or societal limitations, (3) in which the limitation is the cause and effect of the psychiatric disorder, (4) in which the psychiatric disorder has a chronic course; and (5) for which coordinated care of mental health care professionals in care networks is indicated to realize the treatment plan (Delespaul et al., 2013).
- FACT-care for at least 18 months is indicated

## **Exclusion criteria**

- Unable to give informed consent
- Insufficient knowledge of Dutch language

## **Sample size**

Based on the meta-analysis of Nordén and colleagues (2012a), a pre-post effect size of Cohen's  $d = .5$  for the primary outcome is expected. With a sample size of  $N=63$  patients per condition, the study is powered at 80% to detect an effect size of Cohen's  $d = .5$  at a two-tailed significance level of .05. With two conditions we would need to recruit  $N=126$ . Taking into account both repeated measures within a person, assuming a within-correlation of 0.6, and clustering of data (teams; assuming an ICC of .05, health centres; assuming an ICC of 0.1), we will need  $N=133$  patients. Assuming a drop-out of 35%, we will recruit a total of  $N=180$ . There will be 18 participating teams over nine Dutch mental health centres (two teams at each site) and based on rates of incoming patients we expect that a mean of  $N=10$  patients over the course of six months is feasible.

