A meta-analysis including 17 studies and a total of 2263 psychotic patients on the effectiveness of the RACT program for psychotic patients showed impressive effect sizes. That is, the study revealed that participation in the RACT program resulted in improved (social skills) functioning, increased well-being as well as a reduction of symptoms when compared to CAU, with effect sizes of respectively  $d = .82$ ,  $d = 0.88$  and  $d = .72$  (Nordén et al., 2012a). The combined measure for the 17 studies and the three outcome parameters yielded a large effect size ( $d = 0.80$ ). A review summarizing the findings of eight RCT's concluded that the RACT program consisting of involving patients and their significant others by clinical microsystem resource groups yielded positive effects on symptoms, functioning and well-being for patients with psychoses and that the method may be of use for patients within the entire psychiatric spectrum (Malm, Lundin, Rydell, Nordén & Norlander, 2015).

Although the RACT program comprises various new elements, the Resource Group (RG) has been classified as a major key component (Jonsson & Malm, 2002; Nordén et al., 2012b). The crucial focus in the RG model is on involving patient themselves and their significant others in the treatment and the treatment goals and on reinforcement of the client's own self-confidence and ability (empowerment). This way, all available resources in and around the patient are mobilized and integrated in order to shape most effective care. However, no study has been performed on the added value of the RG method. To isolate the RG as the potential declarative mechanism of the promising results of the RACT program, further research is needed. Moreover, knowledge is lacking about the effectiveness for patients within the entire psychiatric spectrum as well as potential obstacles and cost-effectiveness of implementing the RG-method in Dutch Mental Health care. Therefore, the present study will test the effectiveness of the RG method, the implementation, costs and meaning in a randomized controlled trial (RCT) in the Netherlands for patients within the entire psychiatric spectrum.

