## **AIMS**

The primary objective of the present study is to investigate the effectiveness of the Resource Groups on patient outcomes compared to care as usual alone for people with severe mental illnesses. It is hypothesized that participation in the RG is associated with increased empowerment, improved well-being and enhanced social and community functioning, when compared to care as usual.

The secondary objective is to investigate whether care as usual with RG is more cost-effective than care as usual alone. The RG method is hypothesized to be more cost-effective on the long term than care as usual.

The third objective is to explore the implementation process of the RG in Dutch mental health care and the deeper meaning for patients; and to assess potential obstacles, bottlenecks and success factors by using a qualitative case-approach.

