### **Comparison group: FACT care as usual**

In the comparison group, patients will receive FACT care as usual. Importantly, patients in this group are also motivated to work on their treatment goals. Moreover, as is regular practice in FACT care, significant others are involved in the treatment and structural problems between patients and their significant others are addressed. However, these aspects are not to be handled according to the structure of the RG-method.

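### The sample size labels its expected effect pre-post (d = .5) but uses it as a between-arm difference, and the protocol does not settle which is meant

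*Protocol*

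**What the plan says.** The Sample size section bases its assumption on a meta-analysis and says that "a pre-post effect size of Cohen's $d = .5$ for the primary outcome is expected". The next sentence gives 63 patients per condition and says that "the study is powered at 80% to detect an effect size of Cohen's $d = .5$ at a two-tailed significance level of .05". Two conditions make 126. The section then allows for a within-person correlation of 0.6 and for clustering by team (ICC .05) and centre (ICC 0.1), which brings the total to 133. Drop-out takes it to 180.

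The hypothesis in Aims is comparative: "participation in the RG is associated with increased empowerment, improved well-being and enhanced social and community functioning, when compared to care as usual". Under Comparison group, controls receive active FACT care, and "patients in this group are also motivated to work on their treatment goals"; their significant others are involved as well. No expected change in the control arm is given anywhere.

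The Background describes the same meta-analysis as showing better functioning, greater well-being "as well as a reduction of symptoms when compared to CAU, with effect sizes of respectively" .82, .88 and .72, with a combined value of .80. These figures are for the whole RACT programme in psychotic patients. No figure is given for empowerment, and no step leads from these values to .5.

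**The concern.** A pre-post effect size, read literally, is a change over time in treated patients. The trial asks a different question: how much more RG patients gain than FACT patients. The two quantities are equal only if the control arm does not change. The sample-size paragraph passes from one to the other with no linking step, so a reader cannot tell what the 80% refers to.

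This calculation is relied on later. The list of changes to the original protocol argues that recruiting 158 instead of 180 did not affect power, because 133 were needed. If the .5 was not the RG-versus-FACT difference, that reassurance fails with it, and a null NEL result would be read as coming from a trial with 80% power for its expected effect.

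**Working it through.** **Inputs from the protocol.** d = .5, two-sided alpha .05, power 80%, 63 per condition and r = 0.6 (Sample size); baseline value in the model (Statistical analyses, Effectiveness RG).

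**Input assumed here.** Control-arm gain c of 0, 0.1, 0.2 or 0.3 SD, in the same SD units as the .5. The protocol gives no value.

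**1. The plan's own figure.** Two independent arms, normal approximation:

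n per arm = 2(1.960 + 0.842)² / 0.5² = 62.8, rounded up to 63.

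The exact t calculation gives 63.8. Power at 63 per arm is 80.1% (normal) or 79.5% (t). The stated 63 is reproduced.

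**2. Does a pre-post formula give 63?** One group, paired:

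n = (1.960 + 0.842)² / 0.5² = 31.4, so 32; the t version gives 33.4, so 34.

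If the .5 is in raw-score SDs with r = 0.6, the standardised change is .5 / √(2 × 0.4) = 0.559 and the t version gives 27.1, so 28. Neither is near 63. The .5 was used as a between-arm difference.

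**3. If the .5 is literally a within-RG change.** The net difference is d = .5 − c.

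- Unadjusted, power ≈ Φ(d√(63/2) − 1.960).
- Baseline-adjusted with one follow-up, the residual SD is √(1 − 0.6²) = 0.8, so power ≈ Φ((d/0.8)√(63/2) − 1.960).
- Baseline-adjusted with the mean of both follow-ups and equal correlations, the residual variance is (1 + 0.6)/2 − 0.6² = 0.44.

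The table gives the t-based values for 63 per arm. The adjusted columns ignore clustering.

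| Assumed control gain (SD) | Net d | Unadjusted | Adjusted, one follow-up | Adjusted, mean of two |
|---|---|---|---|---|
| 0 | .5 | 79.5% | 94% | 99% |
| 0.1 | .4 | 61% | 80% | 92% |
| 0.2 | .3 | 39% | 55% | 71% |
| 0.3 | .2 | 20% | 29% | 39% |

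**4. How far the adjusted columns can be trusted.** The Sample size section counts the repeated-measures gain and the clustering loss together and ends at 133, which is 133/126 = 1.056 times the unadjusted total. On the plan's own accounting the gain is therefore already spent on clustering. The adjusted columns are optimistic to the extent that clustering matters, and they are not exact power figures for the planned model.

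**5. If the .5 is the between-arm difference.** The first row applies, and 80% in the stated formula is correct.

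**The case against.** The strongest reply is that nothing is miscalculated. The power sentence itself does not say pre-post, and 63 per condition is right for a between-arm d of .5. Pre-post can also be loose wording for a difference between arms in pre-to-post change. The Background favours that reading, since it reports the source only as comparisons with usual care. A net .5 would then be a cautious discount from .72 to .88, whereas a total within-RG change of .5 would be smaller than the net effects in the source. This stands as a possible reading, so the label cannot be treated as proof that a within-arm figure was used. It does not clear up the text: the label says something else, .5 appears nowhere among the source figures, and empowerment is not among the source outcomes.

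A reader might infer something stronger: that the stated 80% holds only if FACT patients do not improve at all, and so that the trial is underpowered. The documents do not support this, for three reasons.

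- The protocol never says that the .5 is a within-arm change.
- Even on that reading, the statement is strictly true only of the unadjusted comparison. The planned model includes the baseline value, and at r = 0.6 with one follow-up it keeps about 80% at a control gain of 0.1 SD, before clustering.
- No control-arm change is given. Active control care makes a gain plausible but does not show one on the NEL. The inclusion criteria require a chronic course, and patients up to 12 months into FACT care may be recruited if intake is slow.

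**Conclusion.** The point holds as an unresolved inconsistency in a key design figure. The expected effect carries a pre-post label, the calculation treats it as a difference between arms, and the cited source as described in the Background does not show which was intended.

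The size depends on the answer. If the .5 is between arms, the 80% stands in the stated formula and the error is one of labelling. If it is the change within RG patients, the 80% does not describe RG versus FACT unless control change is negligible. Assumed gains of 0.1, 0.2 and 0.3 SD then bring power to 61%, 39% and 20% in the plan's own formula, or to about 80%, 55% and 29% with baseline adjustment and one follow-up, before clustering. These losses rest on the assumed control gains and on a common SD scale. They show what the ambiguity could cost; they do not establish that the trial lacks power.

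**What to change.** In Sample size, replace the pre-post effect size with the between-arm NEL difference assumed, in SD units and at a named time point, and say how it was obtained from the cited effects. Reconcile that statement with the account of the meta-analysis in the Background. If .5 is a within-RG change, state the FACT-arm change assumed, subtract it, and give the power for the net difference.

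The section could instead report the smallest between-arm difference detectable with 80% power under the planned mixed model. That figure should include the stated team and centre clustering. At N = 126 and r = 0.6, leaving clustering out gives about 0.40 for one follow-up and 0.33 for the mean of two, so those values should not be quoted as they stand.

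The cost is a rewording and one recalculated figure. No change in N and no extra data are needed. The downside is that the stated power may look less favourable, and the statement that recruiting 158 left power unaffected would have to be checked against the restated effect.

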## **SMALL CHANGES MADE TO THE ORIGINAL PROTOCOL dd. 6th June 2021**

- **COVID-19:** Due to COVID-19, the last 50 assessments of the 18-months follow-up measurements were made by phone/videocall.
- **Sample size:** We planned to include 180 participants. Our power calculations showed that 133 was needed in order to take possible drop-out into account. Our final sample included 158 participants, but our drop-out was less than anticipated. Thus although our sample size was smaller, this did not have an effect on the power of the analysis.
- **Participating centers and teams:** We had planned to recruit patients in nine mental health care centers throughout the Netherlands, with each center agreeing on participating with two teams at the time of writing the protocol. However, one team declined to participate, and there were 3 centers that included an extra team. Thus, recruitment took place at nine mental health centers, with a range of 1 to 3 teams per center.
- **Included patients per team:** We expected to reach a mean of N = 10 participants per team with a range of 6 to 14. There were however two teams that only recruited two patients, and there was one team that included 18 patients. Our range of patients per team was hereby larger than expected.

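### At the protocol's own 35% drop-out, 180 recruits leave 117 patients and not the required 133, and the later statement that 158 recruits left power unchanged is unsupported

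*Protocol*

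**What the plan says.** The Sample size section of the protocol builds its figure in four steps.

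1. It assumes "a pre-post effect size of Cohen's" .5 on the primary outcome. With 63 patients per condition, "the study is powered at 80% to detect an effect size of Cohen's" .5, "at a two-tailed significance level of .05".
2. "With two conditions we would need to recruit" 126.
3. Repeated measures ("assuming a within-correlation of 0.6") and clustering (ICC .05 for teams, 0.1 for centres) raise this to 133.
4. "Assuming a drop-out of 35%, we will recruit a total of" 180. The same paragraph plans 18 teams with a mean of 10 patients.

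The section on small changes to the original protocol returns to the subject once recruitment is over: "Our power calculations showed that 133 was needed in order to take possible drop-out into account". It reports a final sample of 158 and a drop-out lower than expected, without giving the rate. It concludes that "this did not have an effect on the power of the analysis".

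**The concern.** Drop-out enters the Sample size section only after 133, so 133 is the number needed at analysis. A recruitment target that allows for 35% loss should leave 133 once 35% are gone, and 180 does not. The 80% power in that paragraph therefore does not follow from the inputs given beside it.

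The list of changes then gives 133 a different meaning, as a number that already contains the drop-out allowance. Read that way, 158 recruits look comfortably sufficient. Read as the Sample size section defines it, 133 must be compared with the patients who supplied follow-up data, and the protocol does not report that number. A reader weighing the trial's result would rely on a reassurance about power that the document does not support.

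**Working it through.** **Inputs, all from the protocol.** Two-sided alpha 0.05; power 80%; d = 0.5; 63 per condition and 126 in total; 133 after repeated measures and clustering; drop-out 35%; target 180 (Sample size). Final sample 158 (list of small changes).

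**Step 1: the starting figure.** n per arm = 2(z₀.₉₇₅ + z₀.₈₀)²/d² = 2(1.960 + 0.842)²/0.5² = 62.8, so 63 per arm and 126 in total. The protocol's figure is reproduced.

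**Step 2: 133 is taken as given.** The protocol shows no formula. One simple route, with three measurements, 10 patients per team and the team ICC only, gives 126 × (1 + 2 × 0.6)/3 × (1 + 9 × 0.05) = 134. That is close, but it leaves out the centre ICC that the protocol says was used, so it does not confirm 133. Nothing below depends on how 133 was obtained.

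**Step 3: the drop-out allowance.**

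| Quantity | Calculation | Result |
|---|---|---|
| Recruits needed for 133 after 35% loss | 133/(1 − 0.35) = 204.6 | 205 |
| Patients left from 180 after 35% loss | 180 × 0.65 | 117 |
| Shortfall against 133 | 133 − 117 | 16 |
| Largest drop-out that 180 tolerates | 1 − 133/180 | 26.1% |

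The 117 is also below the unadjusted 126. Multiplying by 1.35 gives 133 × 1.35 = 179.6, which rounds to the stated 180. But 18 teams × 10 patients is also 180, so the cause of the error is an inference. The shortfall is the same either way.

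**Step 4: power on this calculation.** If 133 gives 80% and drop-outs contribute nothing, power at n patients is Φ[(1.960 + 0.842) × √(n/133) − 1.960]. At n = 117, √(117/133) = 0.938, so power is Φ(2.628 − 1.960) = Φ(0.668), about 75%.

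**Step 5: the 158 recruits.** To keep 133, drop-out may be at most 1 − 133/158 = 15.8%, that is 25 patients. A drop-out known only to be below 35% leaves more than 158 × 0.65 = 102.7, so anywhere from 103 to 158 patients. The required 133 lies inside that range, so the protocol's own information does not settle whether it was reached.

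**The case against.** The strongest reply is that the arithmetic slip need not have cost the trial any power. The Effectiveness RG section plans a multilevel mixed model on all patients with the baseline value included. A patient with 9-month data only still contributes, so counting every drop-out as zero is a worst case. Baseline adjustment may also add precision. As an illustration, suppose 0.6 also holds between baseline and a single follow-up (an assumption). The variance factor is then 1 − 0.6² = 0.64. With 117/18 = 6.5 patients per team, the team inflation is 1 + 5.5 × 0.05 = 1.275, and the effective number per arm is 58.5/(0.64 × 1.275) = 71.7. Power for d = 0.5 is then Φ(0.5 × √(71.7/2) − 1.960), about 85%. In addition, allocation is stratified by team, so the arms are compared within teams and the team inflation is itself cautious.

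Much of this stands, and it rules out calling the trial underpowered. It does not repair the text. The protocol does not say what its 0.6 represents, and if 133 already includes a gain from baseline adjustment, that gain cannot be counted twice. The Sample size section treats drop-out as patients lost, and the list of changes does not appeal to the model.

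A second reply is that a list of changes naturally differs from the plan. That is fair for 158 against 180. It does not cover the meaning of 133, which the list presents as a result of the same power calculation.

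A reader might also take the pre-post label on d = .5 to mean a within-arm change, so that any improvement among controls would cut the power sharply. The documents do not support this. The Background reports the cited meta-analysis effects as comparisons with care as usual, and 63 per condition is the two-sample size for a between-condition difference of 0.5. At most the label needs clarifying.

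**Conclusion.** The concern holds as an error in the stated derivation and as a contradiction over what 133 means. At 35% drop-out, 180 recruits leave 117 patients, 16 short. The matching target is 205, and 180 allows about 26% loss. The fall from 80% to about 75% rests on two assumptions: that 133 gives exactly 80%, and that drop-outs contribute nothing.

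The statement that 158 recruits left power unaffected is unsupported, which is not the same as wrong. It is correct on the protocol's own calculation if at least 133 patients had follow-up.

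A reader might infer more: that the trial was in fact underpowered, or that only 103 of the 158 remained, with power near 69% by the formula of step 4. The first does not follow, because the planned model may recover some or all of the loss. The second applies the full 35% drop-out, which the protocol says did not occur.

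**What to change.** - **Sample size section.** Say either that 180 recruits allow for 26% drop-out, or that 180 recruits with 35% drop-out give 117 completers and about 75% power on this calculation.
- **List of small changes.** Say that 133 is the number needed at analysis, before any allowance for drop-out. Give the number of the 158 who contributed follow-up, and base the power statement on that number. If the sponsor wishes to rely on partial data or baseline adjustment, state this with the correlation assumed.
- **Effect size.** Say that d = .5 is the assumed between-condition standardised difference, if that is what was meant.

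The cost is a few sentences and one count that the trial team should already hold. Recruitment is complete, so no change in enrolment is asked for. The stated power may become slightly less favourable.

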### **Design and Allocation**

The study is a multicenter randomized clinical trial (MRCT), including 180 patients of nine Dutch mental health care centers.

An independent statistician of the Trimbos Institute will generate a computerized allocation list, stratified on mental health care centers and teams. That is, for each team of every mental health care center a separate allocation sequence will be generated by means of allocation blocks assuming a maximum of fourteen participants per team. Two sizes of allocation blocks are used (i.e. 2 and 4), yielding three possible cells (i.e.: 2x4 and 2x2; 1x4 and 5x2; 0x4 and 7x2). These cells in turn, are randomized to keep the allocation unpredictable for the different stakeholders (care-givers and researchers). In order to minimize the risk of imbalance between conditions, the ratio of these possibilities will be stratified on resp. 1:2:2. The allocation sequence will be stored with the independent statistician and is concealed from all researchers, caregivers, and participants. Once allocated, condition is passed on to the central researcher and local staff by email so that the local intake procedure can be continued. Further matching between patient and case manager is allowed and performed by the local staff of the FACT-team. At start of the baseline measurement (0 months), written informed consent is obtained. Further assessments take place 9 (T1) and 18 (T2) months after obtaining informed consent.. Local independent research assistants will carry out all assessments. Assessments comprise self-report questionnaires (administered on PC) and interviews, see Table 1 and Table 2. Given the nature of our study, blinding of participants and treating clinicians is not possible. The local research assistants however are blinded. To optimize similarity in assessments, research assistants use an extensive standardized study protocol and discuss process in regular telephonic and face-to-face meetings with the central researcher.

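### The 35% drop-out allowance was added to the number needed rather than divided out, so a target of 180 covers about 26% drop-out and leaves 117 patients, not 133, at 35%

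*Protocol*

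**What the plan says.** The Sample size section of the protocol builds its target in three steps.

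- **Base number.** It takes 63 patients per condition (126 in total) and says that "the study is powered at 80% to detect an effect size of Cohen's" 0.5 "at a two-tailed significance level of .05".
- **Adjustment.** It allows for repeated measures ("assuming a within-correlation of 0.6") and for clustering by team (ICC 0.05) and by centre ("health centres; assuming an ICC of 0.1), we will need"). The result is 133 patients.
- **Drop-out.** It then states "Assuming a drop-out of 35%, we will recruit a total of" 180.

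Design and Allocation carries the same total, describing a trial "including 180 patients of nine Dutch mental health care centers". The later section on small changes to the original protocol reports: "Our final sample included 158 participants, but our drop-out was less than anticipated". From this it concludes that the smaller sample did not affect power.

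**The concern.** The number needed, the drop-out rate and the number recruited cannot all be right together. The 133 is the number required before drop-out is considered, so it should be what remains after 35% of recruits are lost. Taking 35% away from 180 does not return 133. It looks as if the rate was applied to the number needed instead of to the number recruited, a slip that always gives a target that is too small.

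At stake is the power claimed for the primary outcome. A reader takes 180 to be a target that keeps 80% power through 35% attrition. If it does not, the planned margin for attrition is overstated. The later reassurance about the 158 patients included is also judged against that margin.

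**Working it through.** **Inputs**, all from the Sample size section unless noted: d = 0.5; two-sided alpha 0.05; power 80%; 63 per arm, 126 in total; 133 after adjustment; drop-out 35%; recruitment 180. Equal allocation follows from the equal numbers per condition. The 158 included comes from the section on small changes.

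**1. Base number.** n per arm = 2 × ((1.960 + 0.842) / 0.5)² = 62.8, rounded up to 63, so 126 in total. This reproduces. Power at 63 per arm is 80.1% by normal approximation and 79.5% by the noncentral t.

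**2. Drop-out step.**

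| Calculation | Result | Gives 180? |
|---|---|---|
| 133 × (1 + 0.35) | 179.55 → 180 | yes |
| 133 / (1 − 0.35) | 204.6 → 205 | no |
| 126 / (1 − 0.35) | 193.8 → 194 | no |

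Of these, only multiplication by 1.35 gives the stated figure.

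**3. What 180 delivers.**

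- Patients left at 35% drop-out: 180 × 0.65 = 117.
- Shortfall: 133 − 117 = 16, and 16 / 133 = 12%.
- Highest drop-out at which 133 remain: 1 − 133/180 = 26.1%.
- Recruitment needed at 35% drop-out: 205, which is 25 more than 180.

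**4. Power at 117.** The protocol's own inflation factor is kept: 133/126 = 1.056. The equivalent number of independent patients is 117 / 1.056 = 110.8, or 55.4 per arm.

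| | 63 per arm (133 patients) | 55.4 per arm (117 patients) |
|---|---|---|
| Power at d = 0.5, t-test | 79.5% | 74.2% |
| Power at d = 0.5, normal approximation | 80.1% | 74.9% |
| Detectable d at 80% power, t-test | 0.503 | 0.537 |

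For the normal approximation at 55.4 per arm: 0.5 × √(55.4/2) = 2.632; 2.632 − 1.960 = 0.672; Φ(0.672) = 74.9%. If the calculation is instead scaled so that 133 gives exactly 80%, power at 117 is 74.8%. Within either method the loss is about 5 percentage points.

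**5. The sample actually included.** With 158 patients, 133 remain only if drop-out is at most 1 − 133/158 = 15.8%. The protocol does not give the observed drop-out rate.

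**The case against.** Five points can be made on the other side.

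- **The trial did not run at 180 with 35% drop-out.** The protocol reports 158 included and less attrition than expected, so the 74% describes a scenario that did not occur. This stands: realised power is unknown and is not shown to be 74%. It does not repair the planning sentence. The section on small changes also leans on the same planning figures to say that power was unaffected. It describes 133 as already allowing for drop-out, whereas in the Sample size section 133 is the number before drop-out.
- **Drop-outs may still contribute data.** The Statistical analyses section plans an intention-to-treat mixed model, and the empowerment list is scheduled at 0, 9 and 18 months, so a patient lost after month 9 still supplies one post-baseline value. This also stands in part: 117 is a completer count, and the model could recover some of the loss. But the protocol adds its drop-out allowance after already allowing for repeated measures, so its own calculation treats drop-outs as lost.
- **The 133 is not derived.** No formula is shown, and the power figures take the factor 133/126 as given. If that factor is wrong, the 80% and the 74% are both wrong. The 26.1% limit needs only the stated 133 and 180, and the mistake in the drop-out step is the same whatever number is needed.
- **The origin of 180 is inferred.** The protocol does not show the multiplication, and 18 teams with a mean of 10 patients also make 180. The explanation is therefore likely rather than documented. The mismatch with 35% exists whichever way 180 arose.
- **35% might have meant 35% of 133.** Nothing in the text says so, and a drop-out rate is ordinarily a share of those entered. If it was meant, the sentence still needs rewording, because the rate among recruits is then 26%.

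**Conclusion.** The concern holds. Under the stated 35% drop-out, 180 recruits leave 117 patients against a stated need of 133; the number consistent with that assumption is 205. The firm result, which depends only on the protocol's own 133 and 180, is that the target tolerates at most 26.1% drop-out.

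The power result, about 74–75% instead of about 80% at d = 0.5, with a detectable effect of about 0.54 instead of 0.50, is conditional on two things: that 133 is the correct number for 80% power, and that drop-outs provide no outcome data. It describes the plan and not the completed trial. The error runs in the optimistic direction and bears on the primary outcome, and nothing elsewhere in the protocol corrects it.

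**What to change.** Correct the drop-out sentence in the Sample size section in one of two ways:

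- state that a target of 180 leaves the required 133 patients at up to 26% drop-out; or
- keep 35% and state that 180 then leaves 117 patients, with about 74–75% power for d = 0.5 (detectable d about 0.54 at 80% power), on the assumptions that drop-outs contribute no outcome data and that 133 is right.

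In either case, 180 should no longer be presented as the number that allows for 35% drop-out. The total in Design and Allocation can stay, since it only repeats the recruitment target.

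The cost is one rewritten sentence and a less favourable stated power or tolerated drop-out. No additional recruitment and no change to design or analysis is asked for.
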